## Abstract

**Background:**

Hwa-byung, a Korean culture-bound syndrome with both psychological and somatic symptoms, is also known as ‘anger syndrome’. It includes various physical symptoms including anxiety, a feeling of overheating, a sensation of pressure on the chest, heart palpitations, respiratory stuffiness, insomnia, and anxiety.

**Methods/design:**

The proposed study is a single-center, double-blind, randomized, controlled trial with two parallel arms: an oriental medicine music therapy (OMMT) group and a control music therapy (CMT) group. In total, 48 patients will be enrolled into the trial. The first visit will be the screening visit. At baseline (visit 2), all participants fulfilling both the inclusion and the exclusion criteria will be split and randomly divided into two equal groups: the OMMT and the CMT (n = 24 each). Each group will receive treatment sessions over the course of 4 weeks, twice per week, for eight sessions in total. The primary outcome is the State-Trait Anxiety Inventory (STAI), and the secondary outcomes are the Hwa-byung scale (H-scale), the Center for Epidemiologic Studies Depression Scale (CES-D), the Hwa-byung visual analogue scale (H-VAS) for primary symptoms, the World Health Organization Quality of Life scale, brief version (WHOQOL-BREF), and levels of salivary cortisol. Patients will be asked to complete questionnaires at the baseline visit (visit 2), after the last treatment session (visit 9), and at 4 weeks after the end of all trial sessions (visit 10). From the baseline (visit 2) through the follow-up (visit 10), the entire process will take a total of 53 days.

**Discussion:**

This proposed study targets patients with Hwa-byung, especially those who have exhibited symptoms of anxiety. Therefore, the primary outcome is set to measure the level of anxiety. OMMT is music therapy combined with traditional Korean medicinal theories. Unlike previously reported music therapies, for which patients simply listen to music passively, in OMMT, patients actively move their bodies and play the music. Because Hwa-byung is caused by an accumulation of blocked emotions and anger inside the body, OMMT, because of its active component, is expected to be more efficacious than pre-existing music therapies.

**Trial registration:**

Current Controlled Trials ISRCTN11939282

## Background

Hwa-byung is a syndrome caused by unrelieved anger accumulated inside the body. As anger builds up in the patient and fails to be released, the patient reaches a breaking point and explodes in anger and rage. These emotions are categorized as ‘fire’ in Korean medicine, hence the name, ‘fire sickness’. In th*e Diagnostic and Statistical Manual of Mental Disorders*, Fourth Edition (DSM-IV) and in the USA, Hwa-byung is named ‘anger syndrome’ and though to be a Korean culture-bound illness. The annual occurrence of Hwa-byung is approximately 4.2 to 11.9%, and often occurs in middle-aged patients. Because the illness is usually caused by stress occurring over a relatively long period, and symptoms continue even in the absence of the factors that caused the unresolved symptoms, many patients think they are unlikely to be cured.

Patients with Hwa-byung are often diagnosed with major depression, anxiety disorders, or somatization disorders. According to a study by Kim
[1], the probability of patients having both Hwa-byung and major depression was 26.9%, and the patient group diagnosed with Hwa-byung based on the Hwa-byung Structured Clinical Interview for DSM-IV (SCID) had significantly increased evaluation indexes of the State-Trait Anxiety Inventory (STAI) the Center for Epidemiologic Studies Depression Scale (CES-D), and the Hwa-byung scale (H-scale) than patients not diagnosed with Hwa-byung. Music therapy has been reported to relax, sedate, and improve vital signs in patients
[2], and is effective when the patient is undergoing, about to start, or just ending invasive medical examinations or procedures
[3,4]. In addition, music therapy has been reported to reduce the level of salivary cortisol
[5]. In Korea, cases have been reported where the symptoms of children with attention deficit hyperactivity disorder were reduced after receiving oriental medicine music therapy (OMMT)
[6], and students with hearing impairment experienced less stress after playing traditional musical instruments
[7].

OMMT is based on the idea that each oriental musical factor contains different energy, or *qi*. Music with different types of *qi* has different qualities that affect the mind and body of the patients. OMMT aims to control *qi* through stimulation by music, and eventually to achieve balance in both the mind and body
[8].

Until recently, clinical study of OMMT was resticted mainly to patients with cerebral infarction and cancer of the blood. Classifying patients in accordance with Sasang body constitutions (four types) and applying OMMT to patients based on their body constitution was reported to significantly improve blood flow to the brain
[9]. Cases were reported in which hemiplegia and walking impairment due to cerebral infarction improved after OMMT
[10]. It has been reported that leukocyte numbers and absolute neutrophil count (ANC) improved in patients with blood cancer after treatment with OMMT
[11]. There have been previous studies on the music therapy for patients with Hwa-byung, but to our knowledge, there has been no clinical investigations into the effects of OMMT on Hwa-byung.

Hwa-byung is linked with emotions such as fury. When a person is unable to release such emotions and reached a certain level of frustration, these emotions accumulate inside the body, leading to the person having an outburst of temper (considered to be a form that resembles fire). OMMT is an active movement therapy that includes movement of the body and instruments. Therefore, treatment with OMMT is expected to produce positive effects for patients with Hwa-byung. None of the previous studies on music therapy for Hwa-byung has included the physical component of movement along with the music.

## Methods/design

### Hypothesis

Our hypothesis is that OMMT will produce superior reduction in the STAI measurements compared with a control music therapy that has no physical component.

### Objectives

The aim of this proposed study is to determine the effectiveness of OMMT compared with the control music therapy (CMT) in Hwa-byung patients, especially the anxiety. The aims are: 1) to produce a clinically significant improvement in the STAI scores of patients with Hwa-byung patients; 2) to measure the effect of OMMT on the levels of salivary cortisol; and 2) to identify changes in scores on the H-scale, the CES-D, the Hwa-byung visual analogue scale (H-VAS) for primary symptoms, and the World Health Organization Quality of Life scale, brief version (WHOQOL-BREF) after OMMT

### Setting

This trial is a single-center, double-blinded, parallel-group randomized controlled trial, which will be performed at the Hwa-byung Stress Clinic, Kyung Hee University Hospital in Gangdong, Seoul. Patients will be recruited through internet advertisements, newspaper advertisements, and official notices posted in the hospital. Patients recruited for the trial will be required to visit the investigational site and sign a written informed consent form. Patients who sign the consent form, who are diagnosed as having Hwa-byung by the Hwa-byung Structured Clinical Interview for DSM (SCID), and who satisfy the inclusion and exclusion criteria will be registered into the clinical trial. The registered patients will be asked to complete the STAI, the H-scale, the CES-D, the H-VAS, and the WHOQOL-BREF. Once 16 patients have been registered randomization will commence, with equal numbers allotted to the the OMMT group and the CMT group. This randomization process will be repeated three times, until 48 patients are divided equally between the two groups. For 4 weeks the patients will receive either OMMT or CMT in groups of eight patients. Patients will complete the H-VAS at sessions 1, 4 and 8 of the trial, and also after session 8 (in week 4). Salivary cortisol will be collected on the day before session 1, and at session 8., and will be collected twice, at 0800 and again at 1700 hours. The time between the screening tests to the end of the trial may vary depending on the patient schedule. From the first session to the last follow-up in week 8, it will take approximately 53 days to complete the study. Figure
1 is an overview of this proposed trial, and Figure
2 is an approximate visit schedule.

**Figure 1 F1:**
[figure not shown]
Study flow chart.

**Figure 2 F2:**
[figure not shown]
Scales assessment schedule.

### Inclusion criteria

The inclusion criteria are as follows.

• Male or female over the age of 20 years.

• Diagnosed as having Hwa-byung using the Hwa-byung SCID for DSM-IV.

• Provided written informed consent.

• Have no problems with communication (for example, reading, writing, listening, speaking).

### Exclusion criteria

The exclusion criteria of this trial are as follows.

• In need of regular medication or psychotherapy.

• Has a severe neurological or psychiatric disorder.

• Has a history of major neuropsychiatric disorder (for example, autism, learning disorder, mental retardation).

• Has had a change in medication of anti-depressants or barbiturates in the past 1 month.

• Is seriously irritable.

• Participated in any other clinical trials in the past one month from the screening day.

• Had a regular mind/body relaxation training in the past 1 year, such as music therapy, qigong, yoga, or meditation.

• Cannot understand written informed consent form or follow this study.

• Presence of mental retardation and mental or emotional problems.

### Assessments

Various assessments will be carried out at specific visits (see Table
1).

**Table 1 T1:** Summary of assessments at procedures (x shows the items to be carried out at each visit)

**Procedure**	**Screening (visit 1)**^**1**^	**Treatment phase**								**Follow-up (visit 10)**

### Interventions

#### Oriental medicine music therapy

The OMMT program entails eight sessions of 60 minutes each, conducted twice a week over a period of 4 weeks, and composed of five different levels of activity.

The first level is abdominal breathing for 5 minutes; patients breathe rhythmically to slow Korean folk rhythms called *Jinyangjo* played by *Daegum*, a kind of traditional Korean flute. The purpose during this portion of the session is to begin breathing control before the start of the therapy itself. Daegum has the quality of decreasing qi.

The second level involves vocalization and sound. Patients are asked to make the sounds of *Kung*, *Duk*, and *Dung*, which are traditional Korean methods of pronouncing rhythm, using their own voice. This portion of the therapy is conducted twice a week for four weeks in a total of eight sessions 10 minutes each.

The third level of treatment is the five-element rhythm therapy, which takes 10 minutes. Patients stimulate five acupuncture points (GB-20, GB-21, PC-6, ST-40, and GB-31) with maracas to the rhythm of music that has the Wood-qi element of the five elements of music. The objective of this portion is to circulate the blood and *qi* using Wood-*qi* music, which has active characteristics when stimulated.

The fourth level is 10 minutes of spreading music therapy, which lets patients play music themselves using *Janggu*, a traditional percussion instrument.

The fifth level is a 10-minute session of relieving music therapy, in which patients beat out a rhythm with wood blocks, which induces Wood-*qi*. This is performed to the rhythm of Wood-*qi* music, which stimulates the liver *qi*.

The last level is singing with abdominal breathing for 15 minutes. Patients make the sounds of ‘mo’ and ‘mi’, out of ‘ma’, ‘me’, ‘mi’, ‘mo’ and ‘mu’, which have *yin* characteristics

#### Control music therapy

The control music therapy program is also carried out for 60 minutes twice a week for 4 weeks, to give a total of eight sessions. Sessions 1 to 4 involve the patients playing different types of traditional music. Each session consists of three or four different types of music and each has the characteristic of reducing *qi*, making people calm, and lightly stimulating the mind from calmness, heartbreaking sadness, and happiness. From session 1 to 4, the music will be different at each session. The music played in sessions 5 to 8 will be the same music played in the session 1 to 4, but the music will be different at each session.

### Outcomes

#### Primary outcome

The primary outcome of this study is the change in the STAI between visit 2 (before treatment and visit 9 (after all sessions are completed).

#### Secondary outcome

The secondary outcome measures are the level of salivary cortisol and the scores on the H-scale, the CES-D, the H-VAS, and the WHOQOL-BREF.

### Safety assessment

All participants will report any adverse events (AEs) experienced during the treatment or follow-up phases. Every AE will be recorded on the case report form (CRF). If the AE is severe and associated with the trial, the participant will be withdrawn from the trial and given medical treatment.

### Sample size

The primary outcome in this trial is the change in STAI between the baseline (visit 2) and after treatment completion (visit 9). The hypothesis is: H0: δ = Δ1-Δ2 < 0 and H1: δ = Δ1-Δ2 ≥ 0, where Δ1 is change in STAI between baseline and visit 9 and the baseline in the OMMT group, and Δ2: is change in STAI between baseline and visit 9 in the control group.

The sample size was calculated based on a *qigong* study of heart disease
[12]. In this study, the participants were divided into two groups: the ‘*qigong*’ and ‘relaxing’ groups. After eight sessions, in the ‘*qigong*’ group, the mean change in STAI-1 was 8.82 and the standard deviation was 10.385, which is in accordance with a two-tailed, α error of 5% and power of 80% shown in the following equation.

(1)$$N=\frac{2{\left(1.96+0.84\right)}^{2}10.385^{2}}{=22}$$

Therefore, we will be randomly assigning 24 participants to each group, assuming a 10% drop-out rate.

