### Statistical method

The primary endpoint is the STAI. Efficacy analysis will be performed both as per protocol (PP; participants completed the trial without any protocol violation) and as intention to treat (ITT; all randomly assigned participants). The PP dataset will comprise all the patients who completed all the treatment sessions and questionnaires, while the ITT dataset will comprise patients who received at least one treatment session.

The independent *t*-test will be used to compare the changes in the STAI between visit 2 (baseline) and visit 9 between the OMMT group and the control group. Analysis of covariance (ANCOVA), using the baseline score as a covariate, will be used to analyze the mean change in the STAI, the H-scale, the CES-D, the H-VAS, and the WHOQOL-BREF, and in salivary cortisol levels between the two groups.

Other issues not included in this protocol will follow the Korean Food and Drug Agency Clinical Statistical Guidelines (Medicine 65625–13353, 2000. 12.29).

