## Discussion

There is no gold standard of measurement for Hwa-byung. However, anxiety is one of the main symptoms of Hwa-byung, and is a symptom with measurable endpoints, which enables doctors to quantify the level. This is why the application of the STAI to measure the level of Hwa-byung was chosen as the primary endpoint.

This study will use listening to traditional music as the therapy for the control group. Traditional music therapy is not specifically a placebo therapy, as it has been reported that traditional music therapy shows effects for a diverse number of psychological disorders. However, there is no doubt that OMMT is different from the listening to traditional music. The OMMT is based on traditional Korean medicinal theories such as the *yin*/*yang* theory and meridian theory. OMMT does not involve the passive listening to music; patients actively move their body, play the instruments, and thereby release stress. Although similar elements of music will be used, the essence of the two therapies is very different.

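### The sample size enters one qigong arm's before-after STAI-1 change as the OMMT-minus-CMT difference, so the stated 80% power applies only to a between-arm difference of about 9 points

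*Protocol article*

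**What the plan says.** The Sample size section sets out the hypothesis as "H0: δ = Δ1-Δ2 < 0 and H1: δ = Δ1-Δ2 ≥ 0", where Δ1 is the OMMT change in STAI from baseline to visit 9 and Δ2 is the control change over the same period. The Statistical method section names the independent t-test for that contrast; it is the test that "will be used to compare the changes in the STAI between visit 2 (baseline) and visit 9 between the OMMT group and the control group".

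The planning figures come from a qigong study in heart disease. In it "the participants were divided into two groups", qigong and relaxing. For the qigong group, "the mean change in STAI-1 was 8.82 and the standard deviation was 10.385". No result is given for the relaxing group, and no difference between the two groups. The error rates are "two-tailed, α error of 5% and power of 80" per cent. The result is 22 per group, and then "we will be randomly assigning 24 participants to each group, assuming a 10% drop-out rate".

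On the comparator, the Discussion says that traditional music therapy is not specifically a placebo, because "it has been reported that traditional music therapy shows effects for a diverse number of psychological disorders".

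**The concern.** A two-sample calculation needs the difference expected between the arms. The change within one treated arm also contains whatever any participant would show over the same period: regression to the mean, attention, the passage of time, and in this trial the effect of an active comparator. All of that cancels in Δ1 − Δ2, but none of it has been removed from 8.82.

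This calculation is the only justification given for 48 participants, and it concerns the primary endpoint. If OMMT's real advantage over CMT is well below 9 points, the trial is much less likely to detect it than the stated 80% suggests. A reader of a non-significant result would then judge it against a power figure that was never worked out for the comparison being made.

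**Working it through.** **Inputs.** From the Sample size section: mean change 8.82 and SD 10.385 (both from the qigong arm), two-sided α = 0.05, power 80%, 22 per group before drop-out and 24 after. From the Randomization section: 1:1 allocation. The control-arm change is not given anywhere, so it is varied below as an assumption.

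**Step 1: reproduce the plan's figure.** The printed equation has no denominator, which may be a typesetting or extraction fault and is not held against the plan. The standard formula is n per group = 2(1.96 + 0.84)² × SD² / δ².

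- Numerator: 2 × 2.8² × 10.385² = 1691.06
- Denominator with δ = 8.82: 77.79
- n = 1691.06 / 77.79 = 21.74, rounded up to 22

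Alternative readings do not give 22: one-sided α gives 18, a single-arm (paired) formula gives 10.9, and the numerator alone gives 1691. Solving back from n = 22 gives δ = √(1691.06 / 22) = 8.77. So 8.82 was used as δ.

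**Step 2: the difference that 80% power requires.** Two-sided t-test with 2n − 2 degrees of freedom and noncentrality δ / (SD × √(2/n)). Solving for 80% power with SD 10.385:

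- 22 analysed per arm: δ = 8.98
- 24 analysed per arm: δ = 8.58

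If OMMT improves by 8.82, then at 24 per arm CMT may improve by 8.82 − 8.58 = 0.24 points before power falls below 80%. At 22 per arm power is already slightly below 80% with no CMT improvement.

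**Step 3: power if CMT improves.** The OMMT change is held at 8.82 and the CMT improvement is assumed, with 4.41 being half of 8.82.

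| Assumed CMT improvement | Difference δ | Power, 22 per arm | Power, 24 per arm |
|---|---|---|---|
| 0 | 8.82 | 78.6% | 82.1% |
| 2 | 6.82 | 56.7% | 60.5% |
| 3 | 5.82 | 44.3% | 47.6% |
| 4.41 | 4.41 | 28.0% | 30.2% |

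The normal approximation behind the plan's formula gives slightly higher values at 22 per arm (80.4%, 58.6%, 46.0%, 29.1%). The pattern is the same.

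**The case against.** Several points can fairly be made for the plan, and some of them limit what can be claimed.

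**Power depends on the difference, not on CMT standing still.** A reader might infer that 80% power holds only if the control group does not improve at all. That is true only if OMMT improves by 8.82, a figure borrowed from another intervention in another disease. If OMMT improves by more, CMT can improve too. The requirement that follows from the calculation is a gap of about 9 points, whatever each arm does. This objection stands, and the point is worded accordingly.

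**The control-arm improvements are assumed.** A reader might take 28%, or any other row, as the trial's true power. The documents do not support that. The Discussion makes zero change hard to assume, but it gives no STAI figure and no result in Hwa-byung. The table shows sensitivity; it does not replace the stated power with another value.

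**The analysis may do a little better than a t-test on 22 per arm.** The ITT set includes anyone with at least one session, so up to 24 per arm may be analysed; the last column covers this. The Statistical method section also names a baseline-adjusted ANCOVA. With an assumed baseline-to-follow-up correlation of 0.5 and equal variances, the residual SD is 10.385 × √0.75 = 8.99. The detectable difference at 22 per arm then falls to about 7.8, and power at a difference of 4.41 is about 36%. That helps, but it does not close the gap.

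**The drop-out step.** A reader might add that 22 / 0.9 = 24.4 calls for 25 per arm. But 22 × 1.1 = 24.2 is a common convention, and 24 fits three batches of 16. Even at 21 per arm, power for 8.82 is 76.6% against 78.6%. This is not a defect worth pressing.

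**The arithmetic itself is sound.** This also stands: 22 follows correctly from the inputs. The fault is that the effect entered is not the quantity in the hypothesis.

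**Conclusion.** The plan is wrong as written on this point. It defines the target as a difference between arms and then sizes the trial on a change within one arm, taken from a study that had a comparator whose result is not used. The stated 80% power therefore applies only to an OMMT advantage of about 9 STAI-1 points (8.98 with 22 analysed per arm, 8.58 with 24), and the article gives no basis for expecting an advantage that large over an active comparator.

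The required difference rests on SD 10.385, a two-sided 5% t-test and equal arms. The power loss for smaller differences rests in addition on assumed control changes. The finding that the wrong quantity was entered depends on no assumed control value.

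**What to change.** Reword the Sample size section so that it:

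1. states that 24 randomised per arm gives about 80% power only for a between-arm difference of about 9 STAI-1 points;
2. says openly that entering 8.82 assumes no change under CMT;
3. replaces 8.82 with the qigong-minus-relaxing difference, if the cited study reports one (the article does not give it, so this step is conditional);
4. gives power for smaller between-arm differences, such as those in the table above, so that readers can judge a null result.

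The trial is already recruiting, and no increase in enrolment is needed. The primary outcome, the test and the conduct of the trial are unaffected. The cost is one reworded paragraph and a less favourable stated power.

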### Randomization

Participants will be randomized during visit 2. The randomization process will be started after 16 patients who passed the screening test are enrolled, and randomization will be carried out three times in total. The steps of the randomization will be overseen by an institution unrelated to this trial. Except for the therapist playing the music, anyone related to the trial (investigators, participants, and monitors) will be blinded to the type of music therapy being used, and the outcomes will be evaluated by the investigators, not the therapist. The first step of the randomization process will be to generate a random number to allocate the patient (SPSS software, SPSS Inc., Chicago, IL, USA). The institution in charge of randomization will label the patients as ‘A’ or ‘B’ and report to the trial center, who will randomize the patients accordingly and assign them to the following sessions. The ratio of the OMMT group and the CMT group is 1:1.

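### With 10% drop-out, 24 per arm leaves 21.6 evaluable, just under the protocol's own 22, so completers-only t-test power is about 78% rather than 80% (minor)

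*Protocol article*

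**What the plan says.** All the planning inputs are in the protocol article. Under Sample size, the source is a qigong trial in heart disease, where in the qigong group "the mean change in STAI-1 was 8.82 and the standard deviation was 10.385". The stated operating characteristics are "two-tailed, α error of 5% and power of 80" percent. The equation uses the normal quantiles 1.96 and 0.84 and arrives at 22. The section then concludes: "Therefore, we will be randomly assigning 24 participants to each group, assuming a 10% drop-out rate". It does not show how 22 became 24.

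Under Randomization, "The ratio of the OMMT group and the CMT group is 1:1". Under Statistical method, the test for the primary outcome is given as "The independent *t*-test will be used to compare the changes in the STAI between visit 2 (baseline) and visit 9". The same section also plans a baseline-adjusted ANCOVA. It analyses two sets: a per-protocol set limited to patients with all sessions and questionnaires complete, and an ITT set, of which it says that "the ITT dataset will comprise patients who received at least one treatment session".

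**The concern.** Two small approximations push in the same direction. The drop-out allowance should leave at least the 22 per arm that the calculation calls for, and 24 randomised per arm does not quite do so. In addition, the 22 comes from a normal-quantile formula, whereas the planned comparison is a t-test, which needs slightly more patients at this size. A reader who takes the section at face value would believe that the primary t-test keeps 80% power after 10% of patients are lost. On the protocol's own inputs it keeps slightly less. What is at stake is the accuracy of the stated power, not the validity of the trial.

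**Working it through.** **Inputs** (protocol article): difference δ = 8.82 and SD σ = 10.385 (Sample size), so δ/σ = 0.849; two-sided α = 0.05; power 0.80; quantiles 1.96 and 0.84; 10% drop-out; 24 per arm; 1:1 allocation (Randomization); independent t-test on the change in STAI (Statistical method).

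**Step 1: reproduce the stated 22.** The denominator of the equation is missing in the text as read, which may be a reading fault and is not part of this point. With δ² in the denominator:

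n = 2(1.96 + 0.84)² × 10.385² / 8.82² = 15.68 × 107.85 / 77.79 = 21.74, so 22 per arm.

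The figure reproduces. A one-sided 5% calculation would give 18, so the two-sided reading is the one used.

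**Step 2: the drop-out step.**

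- Expected completers: 24 × 0.9 = 21.6 per arm, below 22.
- 22 / 0.9 = 24.4, so 25.
- 22 × 1.1 = 24.2, so 25.
- 21.74 / 0.9 = 24.2, so 25.
- 21.74 × 1.1 = 23.9, so 24.

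Only the last route gives 24, and it still leaves 21.6 completers.

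**Step 3: power by number analysed.** The normal formula is Φ(δ / (σ√(2/n)) − 1.96). For n = 21.6, √(2/21.6) = 0.3043, σ × 0.3043 = 3.160, and 8.82 / 3.160 = 2.791; then Φ(0.831) = 79.7%. The t-test column uses the noncentral t distribution with 2n − 2 degrees of freedom and the same noncentrality δ / (σ√(2/n)).

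| Analysed per arm | Normal formula | t-test |
|---|---|---|
| 21 | 78.6% | 76.6% |
| 21.6 | 79.7% | 77.8% |
| 22 | 80.4% | 78.6% |
| 23 | 82.1% | 80.4% |
| 24 | 83.7% | 82.1% |

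Averaging over binomial drop-out of 10% in each arm, instead of fixing 21.6, gives 79.5% (normal) and 77.6% (t-test).

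**Step 4: split the shortfall.** The drop-out step alone costs 80 − 79.7 = 0.3 points. With the t-test as well, the total is 80 − 77.8 = 2.2 points. For the t-test, 23 evaluable per arm are needed, and 23 / 0.9 = 25.6, so 26 randomised per arm. The stated 24 is one patient per arm below the rounding-only figure (25) and two below the t-based figure (26).

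**The case against.** The best defence is that this is rounding-level. The 22 reproduces, 79.7% is 80% to the nearest percent, and the normal formula is a standard planning approximation that the article shows openly. All of that stands, and it is why the point is minor.

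Three stronger readings are tempting, and the document supports none of them.

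- *That the inflation was rounded down.* The article prints no inflation formula, and 21.74 × 1.1 = 23.9 rounds up to 24. How 24 arose is unknown; only the resulting 21.6 is certain.
- *That 80% power and 10% drop-out cannot both hold at 24 per arm.* This is shown only if drop-outs leave the analysis. The ITT set is not limited to completers, and with all 24 per arm analysed the t-test has 82.1% power. The planned ANCOVA may also add precision, but the article gives no baseline correlation from which to compute the gain.
- *That the trial is too small for its real target difference.* The article attributes 8.82 to the qigong group and gives no change for the relaxing group. Power for the actual between-group difference cannot be computed from it in either direction.

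The ITT argument does not remove the point. An allowance for drop-out itself presumes that drop-outs do not contribute, and the per-protocol analysis excludes them by definition. Table 1 schedules no STAI between visits 2 and 9, so a patient lost before visit 9 has no post-baseline value for the primary outcome. How such patients are handled may be set out in a document that is not shown, and its absence here is not counted as a fault.

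**Conclusion.** The point holds as a minor one. On the protocol's own drop-out premise, 24 per arm yields 21.6 evaluable against a stated need of 22. Power is then 79.7% on the protocol's formula and 77.8% for the planned t-test, against the stated 80%.

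This rests on a between-group difference of 8.82, a common SD of 10.385, a two-sided 5% test, 10% loss in each arm and no contribution from those lost. If everyone is analysed, the t-test exceeds the target. The percentages are conditional on 8.82 being the difference between arms, which the article assumes rather than shows. They should not be read as the trial's true power.

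**What to change.** Keep 24 per arm, which fits the three randomisation rounds of 16 (3 × 16 = 48) and the treatment groups of eight. Replace the normal-quantile power statement in the sample size section with a t-based one, for example:

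*If the between-group difference in STAI change is 8.82 (SD 10.385), 24 per arm gives about 78% power by two-sided 5% t-test when 10% are lost and about 82% when all are analysed. The value 8.82 is an assumed between-group difference; the source value is a change within its qigong group.*

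The cost is a short rewording of one section. The stated power with drop-out falls by about 2 points, and no patient, visit or analysis changes.
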